### Statistical analysis

#### Sample size

##### Sample Size Determination and Power Analysis

The proposed sample size was calculated with two objectives in mind: 1) to remain realistic in terms of recruitment based on our anticipated patient flow and the proposed time frame; and 2) to ensure the power to detect significant group differences in the primary outcome measures. Based on our average patient intake of 8-12 new patients a month and the parameters of our existing population, we estimate that we will be able to recruit 3-4 per month in the target age group (12-17) to participate in this pilot study, or a minimum *N *of 50. About 70% will be girls, 30% boys. The majority will be non-Hispanic white, but about 33% will be from other ethnic groups or of mixed-race. The second objective in calculating the proposed sample size is to ensure adequate power (.80) to detect variable relationships (two-tailed, *p *< .05) when conducting the primary analyses. Since there have been no comparable studies of peer mentorship interventions and there are no data available to calculate effect sizes for adherence to skill-based therapies in a pediatric chronic pain population, we have chosen the conservative strategy of extrapolating from other studies of pediatric pain that have used the Functional Disability Inventory (FDI) [39] as an outcome measure in evaluating a CBT-based intervention, in making our power calculations. One study [45] included 30 adolescents with fibromyalgia randomized to either 8 weeks of coping skills training or control (self-monitoring) and then crossed-over to the alternate condition. For the FDI, the authors reported overall effect sizes of 1.29 for patients (n = 14) who received the self-monitoring first and then the coping skills training and 0.52 for patients (n = 13) who received the coping skills training followed by self-monitoring. A second study examined an 8 week CBT trial in 44 adolescents with fibromyalgia [46]. These authors found a significant reduction in the FDI following treatment compared to waitlist control, with an effect size of 0.75. Using the smallest effect size reported in these two studies (i.e., .52), which corresponds to a medium sized effect according to the conventions proposed by Cohen [47], with power of .80 to detect a significant difference in FDI scores using two-tailed tests and with alpha set at .05, it is estimated that we will be able to detect this effect size with 29 subjects per group.

We expect to recruit 4 - 6 mentored participants for each two-month cycle during the active intervention period of 16 months, yielding approximately 32 - 48 mentored participants, with a corresponding number of controls, and seven mentors, giving a total study enrollment number of 70 - 100.

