##### Primary Analyses

The primary outcomes are adherence (percent of sessions attended, percent of home exercises completed). The primary analysis method is repeated measure analysis of variance (ANOVA) between the two groups or the non parametric equivalent (Friedman procedure). We will subtract baseline value from the 2- and 4-month assessment values and use residualized change scores from baseline as the outcome. We will use the Tukey-Fisher criteria for post hoc mean/median comparisons under the ANOVA or Friedman model. The same methods will be used for the analyses on NRS and FDI scores.

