## Discussion

This is an exploratory pilot study in which good evidence of outcome intervention will depend on the success of a mentor training program which is still in development. We have tried to plan all aspects of recruitment and training carefully, but mentor retention and mentor adherence to a structured intervention protocol may vary with factors we have not considered. We will be evaluating carefully the scheduling, format, and content of communications, as well as the attrition rate for the control group at both assessment timepoints. We considered using electronic communication because of its greater flexibility, but phone communication was selected because it will promote social interaction for those patients who may have stopped attending school and other activities outside the home. Peer group therapy is another alternative to introduce peer modeling and reinforcement into a treatment program to improve functioning; but our experience suggests that group meetings often prove impractical for adolescents and families with busy daily schedules. Sample size has been estimated based on other studies of pediatric pain that have evaluated CBT-based interventions and reported a large effect size. We may not have the same effect size and may have underpowered this pilot study. Finally, some patients' participation in recommended therapies may be limited by factors, such as insurance authorizations, over which we have no control.

This exploratory pilot study will enable us to refine the features of the peer-mentorship model - mentor training, structure and content of the manual and protocol, length and format of interactions - and to test our hypotheses that mentors and mentored participants will find this intervention acceptable and that mentored participants will demonstrate improved functioning in comparison to a usual care control group by follow-up. These findings will be disseminated in papers submitted to peer-reviewed journals. We then plan to test the refined model in a controlled R01 trial with a larger sample and longer-term subject follow-up, with a mediator/moderator model.

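### The FDI planning effect of 0.52 comes from a single crossover sequence, so it does not support 80% power for a mentored-versus-control difference with 29 per group

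*Protocol article*

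**What the plan says.** Under Sample Size Determination and Power Analysis, the protocol article says there are no data on effect sizes for adherence, so it plans on the FDI from two earlier studies in adolescents with fibromyalgia.

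- The first study had 30 adolescents "randomized to either 8 weeks of coping skills training or control (self-monitoring) and then crossed-over to the alternate condition". Its FDI results are given by sequence. For the sequence that began with training, the value is "0.52 for patients (n = 13) who received the coping skills training followed by self-monitoring". For the sequence that began with self-monitoring (n = 14), the value is 1.29.
- The second was an 8-week CBT trial in 44 adolescents, with a "significant reduction in the FDI following treatment compared to waitlist control, with an effect size of 0.75".

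The section then proceeds by "Using the smallest effect size reported in these two studies (i.e., .52"), which it classes as a medium effect, and describes its strategy as conservative. It concludes, "with power of .80 to detect a significant difference in FDI scores using two-tailed tests and with alpha set at .05", that 29 subjects per group suffice. Its stated aim is power for differences between groups.

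The trial itself has parallel groups. The Randomization section describes blocks of 4 giving equal mentoring and control groups, and Primary Analyses specifies "repeated measure analysis of variance (ANOVA) between the two groups" on residualized change from baseline, with the same methods for FDI. The Discussion warns that the pilot may be underpowered because the effect may differ, and describes the source studies as having "evaluated CBT-based interventions and reported a large effect size".

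**The concern.** In a two-sequence crossover, a comparison of the two randomized groups gives one number at each time point. The article reports two overall values, each attached to the patients of one sequence. They must therefore describe what happened within each sequence. Each could be a change over time or a within-patient difference between training and self-monitoring. Neither compares one set of patients with a different set.

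The plan nevertheless treats 0.52 as the standardised difference between two independent groups, and describes no conversion. It also ranks 0.52 beside 0.75, which is quoted as a comparison with a control group, and picks the smaller. The two are different quantities, so the ranking does not establish caution.

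What is at stake is how the FDI result will be read. A null result could be taken to exclude a between-arm difference of 0.52 with 80% power, which the stated inputs do not support. Correcting only the arithmetic, by keeping 0.52 and raising the number per group, would carry the same unsuitable input forward, possibly into the larger trial that the Discussion plans.

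**Working it through.** **Inputs from the protocol article.** Effect sizes 0.52 (n = 13, training first), 1.29 (n = 14, self-monitoring first) and 0.75 (versus waitlist); two-sided alpha .05; power .80; 29 per group; equal allocation. Group sizes to consider: 25 (half of the stated minimum N of 50), 29, and 32 to 48 (the expected number of mentored participants, with as many controls).

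**Step 1: try to reproduce 29 per group at 0.52.** The normal-approximation formula for two independent means is n per group = 2(1.96 + 0.84)² / d². With unrounded quantiles the squared sum is 7.849.

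- d = 0.52: 2 × 7.849 / 0.2704 = 58.05, so 59 per group.
- Two-sample t-test: 59.03, so 60 per group.

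The stated 29 is not reproduced.

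**Step 2: what does give 29?** Several calculations do or come close.

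| Calculation | n |
|---|---|
| One group, paired, normal formula, d = 0.52: 7.849 / 0.2704 | 29.03 |
| One group, paired t-test, d = 0.52 | 31.0 |
| Two-sample t-test, d = 0.75 | 28.9 per group |
| Two-sample normal formula, d = 0.75: 2 × 7.849 / 0.5625 | 27.9 per group |
| Two groups adjusted for baseline, d = 0.52, r about 0.71: 58.05 × (1 − r²) | 29 per group |

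The article states no baseline correlation and does not say which calculation was used. The match to 29.03 fits a one-group formula but does not prove that one was used.

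**Step 3: power that 29 per group delivers (two-sample t-test, unadjusted).**

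- d = 0.52: 49.5%
- d = 0.75: 80.1%

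**Step 4: between-arm effect detectable with 80% power, two-sided .05, unadjusted, complete data.**

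| Per group | Detectable effect (SD) |
|---|---|
| 25 | 0.81 |
| 29 | 0.75 |
| 32 | 0.71 |
| 48 | 0.58 |

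None of the group sizes that the article mentions reaches 0.52 on this basis.

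**Step 5: illustration only.** Suppose 0.52 is a pre-to-post change and usual-care controls improve by 0.1 to 0.3 SD on the same scale. Both are assumptions; the article gives neither. The between-arm effect would then be 0.52 − 0.1 = 0.42 down to 0.52 − 0.3 = 0.22. Power would be 35% to 13% at 29 per group, and 63% to 22% at 60 per group. If 0.52 is instead a within-patient training-minus-self-monitoring difference, this subtraction does not apply.

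**The case against.** The strongest reply is that the article does not say how 0.52 was computed. A reader might infer that it is a pre-to-post change with no control contrast, inflated by natural improvement and regression to the mean and scaled on that group's own variability. The article does not support this. Every patient was to have both training and the self-monitoring control, so a within-patient difference between conditions is equally possible, and that would contain a control contrast. This part of the reply stands, and it is why Step 5 is only an illustration.

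Second, a reader might infer that the planned sample is too small. That does not follow from this point. On the article's own figures 0.52 is lower than the one effect quoted against a control group, and planning on 0.75 returns about 29 per group. This also stands. It does not validate the power claim at 0.52, and 0.75 is itself CBT versus waitlist rather than peer mentoring versus usual care.

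Third, the 49.5% reflects the mismatch between 0.52 and 29 per group in a two-group test, which is an arithmetic fault in its own right. That is correct. The two faults are distinct but sit in the same sentence and need one repair.

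Fourth, the planned analysis adjusts for baseline, so unadjusted figures may understate power. True in principle, but the article states no correlation from which a gain could be credited.

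Last, this is an exploratory pilot, Primary Analyses names adherence as the primary outcome, and the Discussion admits possible underpowering. That tempers the weight of the point. The caveat concerns an uncertain effect size, however, and does not tell the reader that the planning value is of a different kind from the effect being tested.

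**Conclusion.** The point holds in a limited form. The planning value of 0.52 is a within-sequence crossover effect. It is not comparable with 0.75 versus waitlist, and it does not support the claim of 80% power for a 0.52 mentored-versus-control FDI difference with 29 per group. Read as a between-arm effect, 0.52 has about half power (49.5%) at that size; 80% is reached only at about 0.75. These figures assume an unadjusted two-sample t-test, equal groups and complete data.

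The between-arm equivalent of 0.52 cannot be derived from the article. The direction and size of any overstatement are therefore unknown, and the point does not by itself condemn the planned number. The fault lies in the stated justification and in how the FDI result would be interpreted. It should be corrected, and the correction is cheap.

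**What to change.** In the sample-size section:

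- State that 0.52 and 1.29 are within-sequence effects from a crossover, and stop using 0.52 as the between-arm planning value. Do not assert that they lack a control contrast unless the source study confirms it.
- Remove the appeal to the smallest effect, and the description as conservative as far as it rests on that ranking.
- Note 0.75 (CBT versus waitlist) as the only between-group effect cited.
- Replace the power sentence with the effects detectable at 80% power, two-sided .05, unadjusted and with complete data: 0.81 at 25 per group, 0.75 at 29, 0.71 at 32 and 0.58 at 48.
- Say that smaller between-arm effects are not powered unless a baseline correlation is assumed and stated, and that FDI will be reported as an estimate with a confidence interval.

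In the Discussion, align the reference to a large effect size with the medium effect named in the sample-size section.

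Make these changes together with the correction of the 29-per-group arithmetic. The cost is wording only, with no extra patients. The drawback is that the stated detectable effect at 29 per group becomes less favourable, about 0.75 instead of 0.52.

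### The stated inputs (effect size 0.52, power 0.80, two-sided 0.05) need 59 to 60 per group in an unadjusted two-group comparison, not 29

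*Protocol article*

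**What the plan says.** The section Sample Size Determination and Power Analysis gives one of its two aims as "to ensure the power to detect significant group differences in the primary outcome measures". Having no adherence data to work from, it borrows FDI effects from two earlier trials in adolescents with fibromyalgia. A crossover trial of coping skills training supplied 1.29 and 0.52, one for each treatment order. A trial of cognitive-behavioural therapy showed a reduction "compared to waitlist control, with an effect size of 0.75".

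The choice among these is explicit: "Using the smallest effect size reported in these two studies (i.e., .52), which corresponds to a medium sized effect". The other inputs follow: "with power of .80 to detect a significant difference in FDI scores using two-tailed tests and with alpha set at .05". The result is "it is estimated that we will be able to detect this effect size with 29 subjects per group".

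The section gives no correlation between visits, number of measurements or covariate gain for this calculation. Elsewhere in the article:

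- Randomization specifies blocks of four, to give two groups of equal size.
- The sample-size section also gives a minimum total of 50. The paragraph after it expects 32 to 48 mentored participants and a matching number of controls.
- Primary Analyses plans a repeated-measures ANOVA of residualized change at 2 and 4 months, and applies the same methods to the FDI.
- The Discussion states: "Sample size has been estimated based on other studies of pediatric pain that have evaluated CBT-based interventions and reported a large effect size". It then allows that the effect may differ and the pilot may be underpowered.

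**The concern.** Every input for a standard two-group calculation is stated, and the output is about half of what those inputs give. A gap of a factor of two is not rounding.

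The FDI is listed under Primary Outcomes, and this is the only power calculation in the article. A reader would take it that the trial has 80% power for a medium effect on the FDI. A non-significant FDI result could then count for more against the programme than it should, including when the larger trial announced in the Discussion is designed.

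**Working it through.** **Inputs.** Effect size d = 0.52 (SD = 1), two-sided alpha 0.05, power 0.80 and 29 per group, from the sample-size section. Equal allocation to two parallel groups, from Randomization.

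**Step 1: the plan's own figure.** For two equal groups under the normal approximation,

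n per group = 2 × (1.960 + 0.842)² / d²

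With (1.960 + 0.842)² = 7.849:

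- d = 0.52: 2 × 7.849 / 0.2704 = 58.05, so **59 per group**. The t-test gives 59.03, so **60 per group**.
- A one-sided test would still need 47 per group (t-test, 46.4).

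The stated 29 is not reproduced.

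**Step 2: what 29 per group delivers (unadjusted t-test).**

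| Per group | Source | Power at 0.52 |
|---|---|---|
| 25 | half of the minimum total of 50 | 43.7% |
| 29 | stated figure | 49.5% |
| 32 | low end of expected recruitment | 53.5% |
| 48 | high end of expected recruitment | 71.3% |
| 60 | t-test requirement | 80.6% |

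The effect detectable with 80% power at 29 per group is 0.749. None of these figures allows for attrition.

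**Step 3: where 29 could have come from.**

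- *The other cited effect.* For d = 0.75 the two-sample t-test needs 28.9, so 29 per group, with power 80.1%. (The normal approximation gives 2 × 7.849 / 0.5625 = 27.9, so 28.)
- *A lost factor of 2.* The one-sample or paired normal formula at 0.52 gives 7.849 / 0.2704 = 29.03. (The paired t-test version gives 31.0.)

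Both land on 29, and the article does not allow a choice between them.

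**Step 4: could the planned analysis justify 29?** The correlations r below are assumptions, since the article gives none. Each multiplier applies to the 58.05 of Step 1.

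- *One follow-up, adjusted for baseline*, multiplier 1 − r²: 29 needs r of about 0.71. With 29 per group, power at 0.52 is about 53% at r = 0.3, 61% at 0.5 and 78% at 0.7.
- *Simple change score*, multiplier 2(1 − r): 29 needs r = 0.75, since 58.05 × 0.5 = 29.03.
- *Mean of both follow-ups, adjusted for baseline, all correlations equal*, multiplier (1 + r)/2 − r²: 32.5 at r = 0.3, 29.03 at 0.5 and 25.5 at 0.6. With 29 per group, power is about 75%, 80% and 85% (normal approximation), if the effect is 0.52 at both visits and the test is of the overall group difference.

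**The case against.** The strongest defence is that the trial will not run an unadjusted comparison at one visit. Primary Analyses plans residualized change over two follow-ups, and Step 4 shows that averaging both visits with correlations near 0.5 brings 29 per group to 80% power. This stands in part: 49% must not be read as the power of the planned analysis. It does not rescue the statement as written, because the sample-size section invokes neither adjustment nor repeated measures and assumes no correlation.

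A second defence is that this is an exploratory pilot, that the article expects more than 29 per group, and that the Discussion concedes possible underpowering. The pilot status and the concession temper the harm. But the concession concerns a true effect that differs from the assumed one, whereas here the unadjusted shortfall exists even if 0.52 is exactly right. The top of the expected range, 48 per group, still reaches only about 71%.

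Three stronger readings are tempting but unsupported:

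- *That the authors really used 0.75.* The t-test match is exact, but the formula for 0.52 without its factor of 2 also gives 29.
- *That the Discussion flatly contradicts the sample-size section.* Its sentence can be read as describing the cited studies, one of which reported 1.29, and not the value used. It is loose wording that sits badly beside a medium 0.52.
- *That the article wrongly calls 0.52 conservative.* That word describes the strategy of extrapolating from other FDI studies, not the value chosen.

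**Conclusion.** The point holds as an arithmetic error in the stated calculation. The article's own inputs require 59 to 60 per group, about twice the 29 given. In an unadjusted two-group comparison, 29 per group has about 49% power at 0.52, and 80% power only for an effect of about 0.75.

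These figures rest on equal groups, a standardised between-group effect and no attrition. They do not show that the planned analysis is a coin-flip, since its power depends on correlations that the article does not give. Nor is there only one way to justify 29: Step 4 gives three, each needing an unstated assumption.

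**What to change.** Do one of the following in the sample-size section:

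1. Restate the figure, for example: *29 per group gives 80% power for d = 0.75 and about 49% for d = 0.52 in an unadjusted two-group comparison; 0.52 would need about 60 per group.*
2. Keep 29, but state the adjusted repeated-measures method and the assumed correlation that give it, with results over a range such as 0.3 to 0.6.

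Under either option, reword the Discussion's sentence on a large effect so that it agrees with the medium 0.52. Report FDI results as estimates with confidence intervals. At 29 per group the unadjusted 95% half-width is about 1.96 × √(2/29) = 0.51 SD, which shows readers how much a null result can exclude. The word *conservative* can stay.

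The cost is wording only, with no extra enrolment. Under option 1 the stated power becomes less favourable.

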### Randomization

Participants recruited for the mentored or control portion of the study will be randomized using a block randomization procedure to assure equal sample sizes in the mentoring and control groups. Using this method allows the groups to have similar numbers of participants in each group at all times. Using a block size of 4, participants are assigned to the appropriate treatment condition as they enroll in the study until the block is completed. Then the following 4 participants are assigned based on the next block [36].

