Prior to working with actual study patients, the best surrogates for the mentors to practice their new skills with are their fellow mentors, who will all be adolescents with resolved or ongoing recurrent pain problems, whose recent experiences have been similar to those of the mentored participants. Each mentor will participate in several different role-playing exercises during training, in which the mentors will break into pairs and improvise conversations that will occur between mentor and mentored participant. For example, they might be told: "One of you will be the mentored participant who has been to a couple of therapy sessions, but is feeling discouraged, like therapy isn't working and probably nothing is going to help. Talk to your partner and choose a specific therapy. Make up a conversation between the two of you, in which the mentored participant wants to give up on therapy and the mentor responds to those feelings. Remember what you have learned about cognitive-behavioral principles in thinking about what the mentor should say." These mock conversations will be observed and critiqued by trainers. Each mentor will be assigned to no more than three mentored participants at any one time; some mentors will only work with one mentored participant during some cycles, to ensure they can take on a mentored participant if one of the group becomes ill or has another emergency. (Additional mentors may be trained during the intervention period if needed due to attrition or higher than anticipated subject enrollment.) During the period of active mentorships (about 18 months), mentors will meet monthly with the research team to review guidelines, provide feedback, and discuss problems that may arise. Mentors will participate in the ongoing iterative process of reviewing and refining the protocol after each cycle.]

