#### Secondary Outcomes

4. ***Anxiety and Depressive Symptoms:***

a. The Child Anxiety Sensitivity Index (CASI), an 18-item scale for measuring anxiety sensitivity. Children rate each item (e.g., It scares me when I feel like I am going to throw up) on a scale ranging from *none *to *a lot *[41].

b. Symptoms corresponding to selected *DSM-IV *anxiety disorders and depression, as assessed by the 47-item, 4-point, Revised Child Anxiety and Depression Scale (RCADS) [42,43].

c. Suicidal ideation will be assessed using a question from the Beck Depression Inventory - 2^nd^ edition (BDI-II) to assess suicidality [44].

For a complete list of measures and time points at which they are administered for each subject group, please see Tables 1 and 2.

**Table 1 T1:** Timetable for study participation for mentored and control subjects

	TIME PERIOD					
	
STUDY PARTICIPATION FOR ADOLESCENT MENTORED AND CONTROL SUBJECTS	Baseline	Week 1-2	Week 3-8	2-month follow-up	Weeks 9-16	4-month follow-up
Measures						

Demographics, NRS & body diagram	X	X	X	X		X

FDI	X	X	X	X		X

CASI	X			X		X

RCADS	X			X		X

BDI-II suicidality	X	X	X	X		X

Treatment tracking	X	X	X	X		X

Interview	X			X		

Estimated Time Required for Study Participation	76 MINS	140-260 MINS	240-420 MINS	86 MINS		56 MINS

**Table 2 T2:** Timetable for study participation for peer mentors

	TIME PERIOD				
**STUDY PARTICIPATION FOR ADOLESCENT PEER MENTORS**	**Months 1-2**	**Months 3-4 (first cycle)**	**Month 5 (break)**	**Months 6-18 (cycles 2-5)**	**Month 19**

Training Sessions	X				

Mentorship Phone Talks and Debriefings		X		X	

Questionnaire Packet	X				X

Assessment and Review Meetings		X		X	

Interview	X				X

Estimated Time Required for Study Participation	7.2-7.8 HOURS	9 HOURS		36 HOURS	70-100 MINS

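### The projected enrolment of 32-48 per arm needs 4-6 recruits a month, but the same section states 3-4; the two agree only at 32 per arm

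*Protocol article*

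**What the plan says.** All references are to the protocol article.

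- **Projection** (Sample Size Determination and Power Analysis, last paragraph): "We expect to recruit 4 - 6 mentored participants for each two-month cycle during the active intervention period of 16 months". The paragraph puts this at about 32-48 mentored participants in all. Adding as many controls and the seven mentors, it arrives at 70-100 people.
- **Recruitment rate** (same section, preceding paragraph): from an intake of 8-12 new patients a month, "we estimate that we will be able to recruit 3-4 per month in the target age group (12-17) to participate in this pilot study". The text equates this with a minimum N of 50.
- **Required size** (same paragraph): 29 per group, for an effect size of 0.52, power .80 and two-tailed alpha .05.
- **Allocation** (Randomization): a "block randomization procedure to assure equal sample sizes in the mentoring and control groups".
- **Cycles** (Table 2, the peer mentors' timetable): a first cycle in months 3-4, a break in month 5, then "Months 6-18 (cycles 2-5").
- **Active period** (Peer Mentor Training): "During the period of active mentorships (about 18 months"), against 16 months in the projection.

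**The concern.** Neighbouring paragraphs give two accrual figures for the same trial. The section names realistic recruitment as the first of its two sample-size objectives, so the projection should follow from the stated patient flow. For most of its range it does not. A reader who takes the 70-100 at face value would expect up to 48 per arm, where the stated rate gives 24-32. The lower part of 24-32 also falls below the plan's own 29 per group, before any loss from dropout or from the rule that removes mentored participants who miss sessions.

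**Working it through.** **1. Reproduce the projection.**
- Cycles: 16 months / 2 = 8.
- Mentored: 8 x 4 = 32 to 8 x 6 = 48. This matches the stated 32-48.
- Randomised, with equal controls: 2 x 32 = 64 to 2 x 48 = 96.
- With seven mentors: 71 to 103. The stated 70-100 is this range rounded.

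**2. Recruitment rate that the projection implies.**
- 64 / 16 = 4 a month to 96 / 16 = 6 a month, against 3-4 stated.

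**3. Enrolment at the stated rate.**

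| Active period | Randomised at 3-4 a month | Per arm | With seven mentors |
|---|---|---|---|
| 16 months | 48-64 | 24-32 | 55-71 |
| 18 months | 54-72 | 27-36 | 61-79 |

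At 16 months the ranges share one point, 4 a month (64 randomised, 32 per arm). At 18 months they overlap from 64 to 72, still well short of 96. At 4 a month, 96 randomised would take 96 / 4 = 24 months; at 3 a month, 32 months.

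**4. Against the required 29 per group.**
- 2 x 29 = 58; 58 / 16 = 3.6 a month.
- At 3 a month for 16 months: 48 / 2 = 24 per arm, five short.
- At the stated minimum of 50: 25 per arm, four short.
- At 4 a month: 32 per arm, three above.

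**5. Power at these sizes** (effect 0.52, two-sided alpha .05, unadjusted two-sample t-test).

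| Per arm | Power |
|---|---|
| 24 | 42.2% |
| 25 | 43.7% |
| 29 | 49.5% |
| 32 | 53.5% |
| 48 | 71.3% |

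On this test, 80% power needs 59.03 per group, so 60. The plan's 29 per group does not reproduce. That is a separate defect, and it limits what can be blamed on accrual: going from 29 to 24 per arm costs 49.5 - 42.2 = 7.3 percentage points.

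**6. Cycles and period.**
- Table 2 lists 1 + 4 = 5 cycles; the projection implies 8.
- Months 3-18 make 16 months only if the break in month 5 is counted as active. The mentor training section says about 18.

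**The case against.** **The low end is attainable.** This stands. At 4 a month for 16 months the trial reaches 64 randomised and 71 in total, inside 70-100. A reader might infer that the projected enrolment cannot be delivered at all; the documents do not support that. What lacks support is the range above the point where the rates meet. The 29 per group also lies within reach of the stated 3-4 a month, though not at its lower end.

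**Table 2 does not fix the number of cohorts.** This also largely stands. A reader might multiply five cycles by 4-6 and conclude that only 20-30 mentored participants are possible. But Table 2 schedules mentors' participation, its cycles 2-5 span 13 months and so are not consecutive two-month slots, and the Intervention section allows staggered cycles. Five against eight remains unexplained in the text, but it is a wording point. Staggering does not raise the number of patients that the clinic supplies each month.

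**Slow accrual is not what takes power below 80%.** Correct. A reader might set 42-53% against the stated .80 and blame recruitment, but the plan's own 29 per group already gives only about 50%.

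**The 3-4 a month might mean mentored participants only.** The text speaks of recruits to the pilot study and ties the rate to a minimum N of 50, which fits the whole study (3 x 16 = 48). Even on the other reading, 3-4 a month would be 6-8 mentored per two-month cycle against the stated 4-6, again meeting at one point only.

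**It is an exploratory pilot.** True. It has feasibility aims, and the Discussion admits that it may be underpowered. This lowers the stakes but does not reconcile the two figures.

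**Conclusion.** The contradiction is real but partial. The projection needs 4-6 recruits a month and the stated patient flow is 3-4. Over 16 months the two agree only at 32 per arm; over about 18 months they agree up to 36 per arm. Beyond that, up to 48 per arm and 100 in total, the stated rate gives no support. At 3 a month, or at the stated minimum of 50, the trial falls four or five per arm short of its own 29, before attrition. The effect of that shortfall on power is modest, from about 50% to 42-44%.

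This rests on 1:1 allocation, on reading the 3-4 a month as all randomised participants, and on a steady rate throughout. The power figures assume an unadjusted t-test; an analysis that uses baseline values could do better. The documents do not settle which recruitment figure is right. The differences in cycle count and in length of the active period are secondary wording points.

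**What to change.** Reconcile the two sample-size paragraphs, Table 2 and the mentor training section to one recruitment rate, one active period and one number of cycles. If cycles overlap, say so where they are counted.

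If the 3-4 a month stands with 16 months, restate expected enrolment as about 48-64 randomised (24-32 per arm) plus seven mentors. Report power or precision at that size: for an effect of 0.52, about 42% at 24, 44% at 25, 50% at 29 and 53% at 32 per arm. If the 4-6 mentored per cycle stands instead, correct the monthly rate and give its basis in patient flow.

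In either case, state separately that 29 per arm does not give 80% power at 0.52, so that this gap is not attributed to accrual.

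The cost is wording only. If the lower rate stands, the stated enrolment becomes less favourable. No extra patients are needed.
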